#### Hypothesis 1: Background and Mechanisms of Stress-Related Exhaustion Disorder

Burnout, a synonym for stress-related exhaustion disorder is a widespread phenomenon, but the underlying mechanisms have not yet been sufficiently explored. In addition, there is no clear distinction between burnout and depression [20,21], and there is currently limited evidence connecting burnout and cognitive functions [22,23]. However, it is known that the reward system in the orbitofrontal brain areas is altered owing to depression and subclinical depressive symptoms, which is evident in electrophysiological correlates [24]. As a result, the perception of mistakes or negative feedback is increased whereas the sensitivity to rewards is decreased [25]. The reward system is based on complex cognitive abilities, the so-called executive functions, which enable goal-directed behavior. Therefore, it is important to compare the effects of burnout and depression using the same parameters and measures and identify similarities and differences with respect to executive functions between the 2 disorders. We expect that individuals with high scores on the burnout scales will perform poorly in cognitive tasks and in tests measuring executive functions, such as working memory, task switching, decision-making, or distractibility. Additionally, we aim to explore possible differences in the resting-state electroencephalography (EEG) and functional MRI brain activity between burnout and nonburnout employees; we expect reduced alpha power and cortical hyperactivity in the former group [26] that may be the neuronal correlate of hypersensitivity to negative events. However, no effects are expected in tasks that measure basal cognitive functions such as vigilance or processing speed. Moreover, a relationship between burnout and immunological parameters [27,28] or metrics of immunological age can be assumed. For example, the concentration of hair cortisol as an index of long-term stress is expected to be positively related to the severity of burnout symptoms and reduced cognitive performance [29,30].

#### Hypothesis 2: Influences of Biological Factors on Cognitive Functioning Over the Lifespan

Considerable progress has been made in recent years to identify biological factors that influence cognition in older adults. These include genetic polymorphisms, such as the brain-derived neurotrophic factor (BDNF) Val^66^Met [31], catechol-O-methyltransferase (COMT) Val^158^Met [32], or latent infectious diseases (eg, *Toxoplasma gondii*) [33,34] that affect brain metabolism. However, studies with young individuals often show no effects [3]. Our hypothesis is that the effects of genes or neuropathologically relevant infections increase with age, which is probably due to the decreasing integrity of neuronal networks as one ages. To test this hypothesis, we aim to compare the performance of young, middle-aged, and old participants with and without infections, such as *Toxoplasma gondii* or COVID-19, or those with a specific gene expression pattern, with the expectation that there are larger inter- and intraindividual differences in the cognitive parameters in older adults compared to younger adults. Moreover, as this is a long-term study, we have the opportunity to test these hypotheses of altered performance in the same individuals over many years. We also aim to identify the immunological age of the participants based on various immunological parameters [35], which will allow us to determine if immunological age rather than chronological age is associated with changes in cognitive functioning.

#### Hypothesis 3: Interaction of Damaging and Protective Factors

Cognitive age is influenced by several internal and external factors. Apart from genetic makeup, environmental and lifestyle variables such as education, type of work, habitual physical and mental activity, nutrition, and stress at work play a modulating role and explain the high degree of variability observed with cognitive performance at advanced ages [36,37]. Thus, we aim to determine which of these factors critically influence the development of cognitive competence and the so-called cognitive reserve in older adults [38]. Consequently, we can discern whether, for example, long-term stress neutralizes the benefits of advanced education on cognitive aging, or whether regular physical activity can compensate for the negative effects of less advanced education. On the other hand, we expect that psychosocial stress (whether during childhood or adulthood) influences immunological or metabolic parameters [39] and that individuals suffering from permanent stress, which has been demonstrated for particular occupational groups, will show corresponding changes in their metabolism and cognition [40].

#### Hypothesis 4: Analysis of Factors Affecting Work Ability Across the Lifespan

As employees age, their physical and mental abilities tend to decline and the risks of accidents at work and work-related diseases increase [41,42]. Work ability is defined as the relationship between individual resources and specific work requirements, and it is the result of interactions between job requirements in terms of physical and mental strain, capacities and skills of the employees, as well as their health status and subjective evaluation of functioning in a given working environment. The instrument used to evaluate the ability to work is the Work Ability Index (WAI) [43]. It considers specific psychosocial and physical factors related to performing a given type of work, as well as the employee’s mental and physical resources. Therefore, it is important to understand the relationships among age, lifestyle, quality of life, work-related factors, stress-related impairments, and cognitive abilities, as well as examine work ability measured by the WAI. Additionally, we will consider individual health risks, such as cardiovascular, metabolic, anthropometric, or immunological contributors to work ability. The longitudinal study design helps assess changes in several risk factors associated with compromised work ability to promote healthy aging in working environments and reduce the likelihood of early retirement.

## Methods

### Study Population

The participants of the Dortmund Vital Study (trial registration number: NCT05155397) represent a sample of a generally healthy population of a western society aged between 20 and 70 years. We define “healthy” in a rather broad sense and allow the inclusion of individuals who are smokers, drink alcohol, are overweight, or have a history of diseases without having severe symptoms. Moreover, we do not impose restrictions regarding education or occupation to enhance the representativity of the sample. Participants are recruited via an internet site, newspaper advertisements, reports and announcements in local print and radio media, public information events, social media, and flyers throughout the city of Dortmund, Germany. In addition, some larger companies in the region were contacted and asked to inform their employees about participating in the study. The number of subjects resulted from a biostatistical estimation (power analysis), in which the size of the expected effects and their variance were considered. The study parameters will be collected repeatedly for 4 time points, namely at the start of the study (baseline), and then 5, 10, and 15 years later (time points for measuring within-subject factors) and between 3 age groups (between-subject factor ie, Age Group: young, middle-aged, and old). Of particular interest here is the interaction between the age group and the measurement time point, which will provide insight into the different trajectories within the specific age groups. Thus, power estimation was conducted exemplarily for repeated-measures analyses of variance (ANOVA) of within-between interactions. The sample size was determined based on a small effect size of *f*=0.1 for the mixed ANOVA model with repeated measures (4 time points) and interactions with the Age Group factor (3 categories), given an error probability of α=.05 and a power of 0.95, resulting in a sample size of 264 individuals (determined with G*Power, a free-source statistical software package) [44]. However, having a larger number of subjects is desirable owing to expected dropouts over the long duration of the study. Therefore, a group size of approximately 600 was targeted, as we assumed a dropout rate of up to 20% per time point of the follow-up measures. Assuming this dropout rate, the number of remaining participants 20 years later would be approximately 300, which roughly corresponds to the estimated sample size, as summarized in Table 1.

**Table 1 table1:** Longitudinal study design showing birth cohorts of the study from 1946 to 1996 with measurements at 5-year intervals^a^.

Birth cohort	Age at T1 2016-2021	Age at T2 2021-2026	Age at T3 2026-2031	Age at T4 2031-2036
1996	20 years	25 years	30 years	35 years
1946	70 years	75 years	80 years	85 years
n	600	480	384	307

^a^The ages of the youngest (20 years old at baseline) and oldest (70 years old at baseline) cohorts and the expected number of subjects at 4 test points (T1 to T4) are indicated.

### Representativeness of the Sample

To verify the representativeness of the sample and thus the generalizability of the future findings, four different aspects are considered:

Age Distribution and Gender: We enroll almost the same number of participants in each age group and compare the proportion in each decade of life (as well as the proportion of women and men) between the participants in this study with the corresponding proportion of the general population in Germany.Genetic Representativeness and Homogeneity: We test whether the distribution of genetic polymorphisms in the sample does not differ from the Hardy-Weinberg equilibrium (HWE).Cognitive Abilities: We test whether neuropsychological tests measuring crucial cognitive functions are comparable with reference values in the literature.Education and Occupation: We compare levels of education and the proportion of employed individuals in the present sample and in the general population in Germany.

First, until August 2021, totally 593 participants have been enrolled. Compared with the average of 20- to 70-year-old people living in Germany [45], the participants of the Dortmund Vital Study are slightly younger (44.2 vs 45.8 years on average), and the proportion of women is higher (61.5% vs 49.6%). The proportions of participants in the Dortmund Vital Study in 5 age groups (20 to 29 years: n = 122, 20.6%; 30 to 39 years: n = 113, 19.1%; 40 to 49 years: n =110, 18.5%; 50 to 59 years: n =146, 24.6%; 60 to 70 years: n =102, 17.2) correspond largely to the proportions in the German population (20 to 29 years: 17.2 %; 30 to 39 years: 19.6 %; 40 to 49 years: 18.2 %; 50 to 59 years: 24%; 60 to 70 years: 21%).

Second, to ensure that the sample of participants of the Dortmund Vital Study is representative for the population in a genetic manner, the HWE is used to compare the expected and observed proportion of common homozygote, heterozygote, and rare homozygote variants of the single nucleotide polymorphisms (SNPs) calculated by the internet-based HWE calculator [46]. A deviation from the HWE was found in only 1 out of the 19 measured SNPs (IL-12), as shown in Table 2.

Third, we compared the scores in the neuropsychological tests between the present study and the corresponding reference or normative values available in the test manuals or literature. The Mini Mental State Examination (MMSE) used for detecting early signs of cognitive impairment shows a mean of 28.1 points (SD 1.9) out of a possible 30 points in our participants aged 60 years and older (n=102) and 28.3 points (SD 1.6) in a healthy sample of 204 participants in the same age range in the study by Votruba et al [47]. For the Beck Depression Inventory, the mean score in our sample is 5.7 points (SD 6.4), which is well below the cutoff for minimal depression (9 points), and similar to the mean of a healthy control group (n=583) described in the test manual, which scored 7.4 points (SD 7.3) [48]. The Multiple-Choice Vocabulary Test (MWT-B) that measures premorbid (crystalized) intelligence shows a mean score of 31 points (SD 3.2) that corresponds to a mean IQ of 115. A healthy control group of adults (n=102) in a study by Satzger et al [49] reached a mean IQ of 121 (the test usually overestimates the IQ obtained with typical intelligence tests). For the digit span test from the Hamburg-Wechsler-Intelligenztest für Erwachsene, Revision (HAWIE-R), the German version of the Wechsler Adult Intelligence Scale-III [50], the mean number of correct responses is 14.1 (SD 3.6) in the present sample and 15.0 (SD 3.2) in a healthy adult sample (n=100) in the HAWIE-R manual [51]. Similarly, the Digit Symbol Test from the same test battery shows a mean score of 59.1 points (SD 12.3) for the Dortmund Vital Study participants and 50.6 (SD 10.3) points in the HAWIE-R manual. For the Stroop Test from the Nürnberger Alters Inventar (NAI) [52], the time to complete the word list for participants aged between 55 to 69 years is 14.7 (SD 2.3) seconds in the present study (n=144) and 16.0 (SD 2.0) seconds in the reference values for healthy older persons in the manual (n=78). For the color naming list of the Stroop Test, the corresponding times are 21.1 (SD 3.7) versus 24.0 (SD 7.0) seconds, and for the interference list, they are 36.7 (SD 7.4) versus 44.0 (SD 13.0) seconds. The capacity for learning new words assessed by the Verbal Learning and Memory Test (VLMT) [53], the German version of the Rey Auditory Verbal Learning Test (RAVLT) [54], shows a mean sum of 54.8 points (SD 4.3), indicating the number of successfully learned words in our sample (n=525), and exactly 54.8 points in a norm sample (n=515) provided in the test manual. Furthermore, the D2 test, measuring selective attention and attentional endurance (D2-R) [55] reveals for our participants aged between 20 and 60 years (n=489), the mean number of correctly crossed symbols is 158 (SD 36.7), whereas the normative value for the same age group (n=976) in the manual is 153 (SD 28.4). Finally, for the 2 subtests from the Leistungs-Prüf-System (LPS, meaning performance test system) validated for people older than 50 years [56], our participants aged 50 years and older (n=217) had a mean of 24.7 (SD 5.1) correct responses in the logical reasoning and 19.5 (SD 6.4) in the spatial rotation subtests, whereas the controls in the LPS manual reached 22.0 (SD 5.2) and 17.6 (SD 6.0) correct responses, respectively.

Fourth, with respect to education, 28% (n=161) of the participants of the Dortmund Vital Study have secondary degree, 30.3% (n=174) have a high school diploma and 41.6% (n= 239) have a university degree, compared to the corresponding proportions in the German population (23.5%, 33.5%, and 18.5%, respectively). Furthermore, 68.6% of the participants in the Dortmund Vital Study are employed (full-, half-, or part-time) compared to 67.7% of the general population in Germany [45].

In summary, we consider the sample of the present study as representative in terms of age distribution, genetics, depressive symptoms, cognitive parameters, and occupation. However, in contrast to the general population, the ratio of female participants and that of university degree holders appear to be higher than in the general population.

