##### Genetic Parameters (SNPs)

Isolation of genomic DNA of leukocytes is performed according to standard procedures [105]. Several genetic polymorphisms potentially related to the structure and function of the central nervous system are selected. The analyzed SNPs are presented in Table 2.

**Table 2 table2:** Single nucleotide polymorphisms measured in the Dortmund Vital Study (N=528) with the number of observed and expected common homozygotes, heterozygotes, and rare homozygotes in parentheses computed using the Hardy-Weinberg equilibrium calculated on the internet [46]^a^.

Genotype	rs (reference SNP^b^ cluster ID)	Allele observed (n)	Allele expected (n)	χ^2^ (*df*)

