**Apo^c^-E2, E3, E4**				
	7412	0=CC (443), 1=CT (83), 2=TT (3)	0=CC (444), 1=CT (81), 2=TT (4)	0.14 (2)
	429358	0=CC (10), 1=CT (127), 2=TT (389)	0=CC (10), 1=CT (126), 2=TT (389)	0.01 (2)
BDNF^d^ Val^66^Met	6265	0=GG (365), 1=GA (148), 2=AA (15)	0=GG (365), 1=GA (148), 2=AA (15)	0.00 (2)
COMT-1^e^	4633	0=CC (128), 1=CT (256), 2=TT (144)	0=CC (124), 1=CT (263), 2=TT (140)	0.45 (2)
COMT-2 Val^158^Met	4680	0=AA (144), 1=AG (256), 2=GG (128)	0=AA (140), 1=AG (263), 2=GG (124)	0.45 (2)
DRD2^f^	6277	0=CC (112), 1=CT (275), 2=TT (141)	0=CC (118), 1=CT (263), 2=TT (146)	1.06 (2)
DRD1^g^-48A/G	4532	0=CC (39), 1=CT (129), 2=TT (93)	0=CC (41), 1=CT (124), 2=TT (95)	0.27 (2)
CHRNA6^h^-1	1072003	0=CC (346), 1=CG (161), 2=GG (21)	0=CC (344), 1=CG (163), 2=GG (19)	0.17 (2)
CHRNA6-3	2304297	0=AA (32), 1=AG (200), 2=GG (296)	0=AA (33), 1=AG (198), 2=GG (297)	0.05 (2)
CHRNB3^i^-1	13280604	0=AA (311), 1=AG (192), 2=GG (25)	0=AA (314), 1=AG (186), 2=GG (28)	0.40 (2)
CHRNB3-2	4950	0=AA (311), 1=AG (191), 2=GG (26)	0=AA (313), 1=AG (187), 2=GG (28)	0.23 (2)
GPCPD1^j^ (EDI3)	6116869	0=GG (198), 1=GT (249), 2=TT (79)	0=GG (198), 1=GT (249), 2=TT (79)	0.00 (2)
GRIN2A^k^	1969060	0=CC (19), 1=CT (165), 2=TT (342)	0=CC (19), 1=CT (164), 2=TT (343)	0.02 (2)
GRIN2A	8057394	0=GG (285), 1=GC (207), 2=CC (36)	0=GG (286), 1=GC (205), 2=CC (37)	0.03 (2)
GRIN2B^l^	890	0=GG (126), 1=TG (254), 2=TT (148)	0=GG (121), 1=TG (263), 2=TT (143)	0.69 (2)
IL^m^-1beta	16944	0=GG (235), 1=GA (221), 2=AA (70)	0=GG (227), 1=GA (237), 2=AA (62)	2.43 (2)
IL-6	1800795	0=CC (85), 1=CG (265), 2=GG (176)	0=CC (90), 1=CG (255), 2=GG (181)	0.78 (2)
IL-12A	568408	0=AA (9), 1=AG (141), 2=GG (178)	0=AA (19), 1=AG (120), 2=GG (188)	*9.53* (2)
TNF-alpha^n^	1800629	0=AA (15), 1=AG (141), 2=GG (372)	0=AA (14), 1=AG (143), 2=GG (370)	0.13 (2)

^a^The chi-square test indicates the conformity between the expected and observed distribution. Significant deviances from the HWE are italicized.

^b^SNP: single nucleotide polymorphism.

^c^APO: apolipoprotein.

^d^BDNF: brain-derived neurotrophic factor.

^e^COMT: catechol-O-methyltransferase.

^f^DRD2: dopamine receptor D2.

^g^DRD1: dopamine receptor D1.

^h^CHRNA6: cholinergic receptor nicotinic alpha 6.

^i^CHRNB3: cholinergic receptor nicotinic beta 3.

^j^GPCPD1: glycerophosphocholine phosphodiesterase.

^k^GRIN2A: glutamate ionotropic receptor NMDA type subunit 2A.

^l^GRIN2B: glutamate ionotropic receptor NMDA type subunit 2B.

^m^IL: interleukin.

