^n^TNF-alpha: tumor necrosis factor-alpha.

In future analyses, we intend to evaluate polygenic scores (PGS) because based on the findings of several recent large-scale genome-wide association studies, it became increasingly clear that thousands of alleles across the genome (polygenic architecture) contribute to interindividual variations in cognitive performance with small effect sizes [19]. DNA genotyping will be carried out using the Illumina Infinium Global Screening Array 3.0 with major depressive disorder and Psych content, and genome-wide PGS (weighted sums of each participant's trait-associated alleles across all SNPs) will be created using publicly available summary statistics for cognitive performance and other available behavioral phenotypes of interest.

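### Hardy-Weinberg tests on 19 SNPs cannot support the stated genetic representativeness or homogeneity; they use no population reference and have low power against small or mildly divergent ancestry mixtures

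*Protocol article*

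**What the plan says.** Under Representativeness of the Sample, the protocol article sets out four checks of representativeness and hence generalisability. The genetic one reads "Genetic Representativeness and Homogeneity: We test whether the distribution of genetic polymorphisms in the sample does not differ from the Hardy-Weinberg equilibrium". Its purpose is given as "to ensure that the sample of participants of the Dortmund Vital Study is representative for the population in a genetic manner". The result is already reported: "A deviation from the HWE was found in only 1 out of the 19 measured SNPs", the exception being IL-12. The summary closing that section then counts genetics among the respects in which the sample is representative.

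Table 2, under Genetic Parameters (SNPs), gives N=528, the observed and expected genotype counts, and a chi-square for each SNP with 2 degrees of freedom. Its footnote says "Significant deviances from the HWE are italicized" but gives no significance level.

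Two later uses of genetic data are affected. Hypothesis 2 states "Our hypothesis is that the effects of genes or neuropathologically relevant infections increase with age". For polygenic scores, named as a future analysis, "DNA genotyping will be carried out using the Illumina Infinium Global Screening Array 3.0". The Data Analysis section names gender and education as examples of confounders and leaves detailed methods to later publications.

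**The concern.** The check is given two jobs, and the test does neither well.

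*Representativeness.* Expected Hardy-Weinberg counts come from the sample's own allele frequencies. A sample whose frequencies are far from those of the German population can fit perfectly. For age, sex, education and employment the article does compare with German figures; for genetics it does not.

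*Homogeneity.* Mixing groups with different allele frequencies lowers the share of heterozygotes, but the shortage depends on the square of the frequency difference and the test statistic on the square of the shortage. Small or mild mixtures are therefore nearly invisible to it.

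At stake is false reassurance for the gene analyses. If groups of different ancestry differ both in allele frequency (or polygenic score) and in test scores, a variant with no effect can appear associated with cognition. If the mix also varies by age group, the same can appear as the gene-by-age effect of Hypothesis 2.

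**Working it through.** **1. Reproducing Table 2.** For counts (x, y, z) with total N and allele frequency p = (2x+y)/(2N): F = 1 - y/(2Np(1-p)), and chi-square = N·F².
- IL-12A (9/141/178): N=328, p=0.242, expected heterozygotes 120.5 against 141 observed. F = 1 - 141/120.5 = -0.17 and chi-square = 9.53, as printed. P=0.002 on 1 df, 0.0085 on 2 df.
- The next highest is IL-1beta at 2.43 (P=0.12 on 1 df).
- The other values agree with the printed ones up to rounding of the expected counts (the largest gaps are 0.18 against 0.14 for rs7412 and 0.45 against 0.40 for rs13280604).

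So 1 of 19 reproduces. The standard degrees of freedom are 3 - 1 - 1 = 1, not the printed 2, but no flag changes. Results below use the 5% cutoff on 1 df (3.84), with the cutoff implied by 2 df (5.99) in brackets. The 5% level is an assumption.

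The single flag is an excess of heterozygotes, the opposite of what mixture produces. Its counts sum to 328, not 528. If 378 had been meant where 178 is printed (an assumption), chi-square would be 1.02 and no SNP would deviate. The printed 9.53 was, however, computed from 178.

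**2. Power against mixture.** Assumed inputs, not in the article: minority share a, allele-frequency difference d, mean frequency p=0.3. From Table 2: n=528.

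F = a(1-a)d²/(p(1-p)); noncentrality = n·F².

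| a | d | F | n·F² | Power per SNP | P(at most 1 flag in 19) |
|---|---|---|---|---|---|
| none | – | 0 | 0 | 5% (1.4%) | 75% (97%) |
| 10% | 0.2 | 0.09×0.04/0.21 = 0.017 | 0.155 | 6.8% (2.2%) | 63% (93%) |
| 20% | 0.2 | 0.16×0.04/0.21 = 0.030 | 0.49 | 10.8% (4.1%) | 38% (82%) |
| 20% | 0.3 | 0.16×0.09/0.21 = 0.069 | 2.48 | 35% (19%) | 0.3% (10%) |

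The last column treats the SNPs as independent and gives all 19 the same d.

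Simulating the whole screen instead, with allele frequencies drawn around those in Table 2 at a given Fst (600 runs each), the chance of at most one flag is:
- Fst 0.01, any share from 10% to 50%: 71-76% (95-97%), about the same as with no mixture.
- Fst 0.05, 10% share: 64% (91%).
- Fst 0.10, 20% share: 11% (32%).
- Fst 0.15, 50% share: under 1% (2%).

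**3. What Table 2 itself says about mixture.** Pooling F over the 19 SNPs weighted by n, with SE = 1/√(Σn):
- All 19: Σn=9,556, F = -0.006, SE 0.010, upper 95% limit -0.006 + 1.96×0.0102 = 0.014.
- Without IL-12A: Σn=9,228, F = 0.000, SE 0.010, upper limit 0.020.

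In the equal-difference model with d=0.2, a 5% share gives F=0.009, inside both limits. A 10% share gives 0.017, above the first and below the second. Shares of 20% and 25% give 0.030 and 0.036, above both.

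**4. Bias in an unadjusted null SNP test.** With an assumed score difference D between groups:

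r = a(1-a)·2d·D / √[2p(1-p)(1+F)·(1+a(1-a)D²)]; rejection rate from Fisher z with n=528.
- a=5%, D=0.3: r = 0.0057/0.652 = 0.0087; z = 0.0087×√525 = 0.20; rejection rate 5.5%.
- a=10%, D=0.5: r = 0.027; rejection rate 9.6%.
- a=10%, D=0.8: r = 0.0288/0.672 = 0.043; z = 0.98; rejection rate 17%.

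**The case against.** The strongest reply has three parts.

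First, a reader might infer that these tests would pass nearly any population mixture. They would not. A 20% minority with a frequency difference of 0.3 leaves at most one flag only 0.3% of the time (10% at the looser cutoff). That stronger reading is unsupported; the weakness is confined to small or mildly divergent mixtures.

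Second, a reader might extend step 4 to shares of 20-25% and obtain false-positive rates of 19% (20% share, 0.5 SD) to 51% (25% share, 0.8 SD). Table 2 contradicts those cases: under the same equal-difference model they need a pooled F of 0.030-0.036, beyond either upper limit. A single SNP could still differ more between groups than the rest, but that is another model. More basically, the article reports no ancestry shares and no score differences by ancestry. Confounding is a conditional possibility, not a demonstrated bias.

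Third, this is a condensed article that defers its methods, and it never presents the Hardy-Weinberg check as the safeguard for association analyses. That stands: the absence of an ancestry adjustment here is not in itself a fault.

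What survives is narrower. The article chose a test, ran it and drew from it a conclusion about genetic representativeness, under a label that also claims homogeneity. No deferred detail changes what that test can show.

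**Conclusion.** The concern holds in limited form. The representativeness conclusion does not follow at all, because no population reference enters the test; this needs no assumption. The homogeneity claim is weakly supported: per-SNP power is 6.8% (2.2% at the cutoff the printed 2 df imply) for a 10% mixture with d=0.2 and p=0.3, both assumed. One flag in 19 is unremarkable with or without such a mixture, and the flag observed points the other way. The pooled F argues against a large divergent mixture but leaves a 5% share compatible and a 10% share borderline.

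For mixtures of 5-10% with score differences of 0.3-0.8 SD, all assumed, a null SNP would be declared significant about 5.5-17% of the time instead of 5%. This applies only if scores differ by ancestry. Polygenic scores are open to the same mechanism.

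**What to change.** - Keep the Hardy-Weinberg tests as a genotyping-quality check only. State the level used and correct the degrees of freedom to 1.
- Check the IL-12A counts against source, since they sum to 328 and show excess heterozygotes. DRD1, at 261, is also well short of 528 and should be explained.
- Withdraw the conclusion that the sample is genetically representative or homogeneous on this basis.
- Once the planned array data exist, derive ancestry principal components, report ancestry outliers, and include the leading components (for example 10) as covariates in SNP and polygenic score analyses. For the gene-by-age hypothesis add component-by-age terms. This reduces confounding by ancestry; it does not guarantee its removal.

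**Cost.** The wording changes cost nothing. The covariates use about 10 degrees of freedom for main effects. With three age groups the interactions add 10 × 2 = 20, about 30 in all, out of 528 genotyped participants. Single-SNP analyses must be re-run when the array data are available.
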